### Control arm

The control group is instructed to keep their PA level constant over the 12 months of the study. Controls do not get informed about their fitness level during the exercise test nor receive any interpretation of the test results unless a finding is detected which requires medical attention. They are not be given an evaluation of their answers to the activity questionnaires nor on their pedometry (or accelerometry) data. At the closeout visit after 12 months, controls receive a pedometer and access to the web-based log and get a PA counselling as the intervention group had received at baseline.

### Recruitment and study procedures

This RCT is currently ongoing. The first patient was enrolled on 16th July 2014 and the estimated study completion date is December 2018.

At enrolment, a clinical assessment is performed for all patients using standardised procedures. Table 1 provides an overview about all study visits and assessments throughout the study. Two baseline visits (1b & 1b) are scheduled to evaluate inclusion and exclusion criteria. Following randomisation on baseline visit 1b, participants are seen every 3-months during the 12-month study period (4 follow-up visits, see Fig. 1).

**Table 1 Tab1:** Data collected at baseline and follow-up

	Baseline		3 month	6 month	9 month	12 month
Visit	1a	1b	2	3	4	5
Time	−21 d (±7 d)	Day 1	90 d (±14 d)^a^	180 d (±14 d)^a^	270 d (±14 d)^a^	360 d (±14 d)^a^
Informed consent	X					
Medical history	X					
In−/exclusion criteria	X	X				
Physical examination, vital signs	X	X	X	X	X	X
Physical (in)activity history	X					
Anthropometry	X	X	X	X	X	X
Spirometry	X	X	X	X	X	X
Body plethysmography	X	X	X	X	X	X
Oral glucose tolerance test		X			X	
Cardiopulmonary exercise testing	X			X		X
Pedometry		X	(X)^b^	X	(X)^b^	X
Physical activity questionnaire (7-day recall)	X	X	X	X	X	X
Exacerbations, upper respiratory tract infections, antibiotic use, adverse events	X	X	X	X	X	X
CFQ-R questionnaire	X			X		X
DASS questionnaire	X			X		X
EMI 2 questionnaire	X			X		X
Diary, 3-months retrospective questionnaire, Interview^c^, Patient-initiated contact	X	X	X	X	X	X
For Intervention group only						
Exercise motivation interview^c^	X	X	X	X	X	X
Web-based diary, paper diary, pedometer^d^	XXXXXX					
Schedule of measurements for the sub-studies in selected centers						
	Baseline		3 month	6 month	9 month	12 month
Visit	1a	1b	2	3	4	5
Time	−21 d (±7 d)	Day 1	90 d (±14 d)	180 d (±14 d)	270 d (±14 d)	360 d (±14 d)
Accelerometry^e^		X		X		X
Multiple breath washout^e^	X	X		X		X
DXA^e^	X			X		X
Scintigraphy^e^	X			X		

*CFQ-R* Cystic Fibrosis Questionnaire-revised, *DASS* Depression and Anxiety Stress Scales, *DXA* Dual energy X-ray absorptiometry, *EMI* Exercise Motivational Inventory

^a^In case of an exacerbation the visit will be postponed until 14 days after oral or intravenous antibiotic treatment of exacerbation has been stopped

^b^Intervention group only

^c^At each visit and at scheduled telephone contacts

^d^Over the whole intervention period of 12 months

^e^In selected centres only

### Study endpoints and measurements

The primary outcome measure is the difference between the changes in FEV_1_ (in % predicted) from baseline (using the average of the two baseline measurements) to 6 months in the intervention group compared to controls. Secondary outcomes include change in aerobic exercise capacity (VO_2_peak), PA, HRQoL and others listed in Table 2. Vital signs, anthropometric characteristics (weight, height, skinfolds) are measured at each study visit using standardised procedures.

**Table 2 Tab2:** Primary, secondary and explorative outcome measures

Outcome	Variable	Measurement
Primary endpoint		
• Lung function	FEV_1_% predicted	Spirometry
Secondary endpoints		
• Exercise capacity	VO_2peak_ % predicted	CPET
	Watt_max_ % predicted	CPET
• Physical activity	Steps per day	Pedometry
	Exercise steps per day	Pedometry
	Reported physical activity (min per day)	7-day recall questionnaire
• Pulmonary function	FEV_1_% predicted	Spirometry, Bodyplethysmography
	FVC % predicted	
	RV/TLC %	
• Exacerbation	Time to first exacerbation	Questionnaire (modified Fuchs criteria) and physician assessment
• Body composition	Body fat	Skinfolds
	Lean body mass	Skinfolds
• Health-related quality of life	Scales	Questionnaire (CFQ-R)
• Depression, anxiety and stress scales	Scales	Questionnaire (DASS)
• Glycaemic control	Plasma glucose concentrations (fasting, 1 and 2 h after standardised glucose load)	Oral glucose tolerance test^a^
Explorative endpoints		
• Physical activity	Moderate and vigorous physical activity	Accelerometry^b^
• Infections	Number of upper respiratory tract infections	3-months retrospective questionnaire, Interviews, Diary and telephone calls
• Antibiotic therapy	Days on additional oral/intravenous antibiotics	3-months retrospective questionnaire, Interviews, Diary and telephone calls
• Body composition	Body mass index	Based on measured height and weight
• Lung function	Lung clearance index	Multiple breath washout^c^
• Mucociliary clearance	Mucociliary clearance	Scintigraphy^d^
Safety endpoints		
• Adverse events	Adverse events at least possibly related to exercise (e.g., sprains, fractures etc)	Judged by investigator
Others		
• Compliance with exercise	Exercise goal of 3 additional hours of vigorous activity per week	Baseline assessment and web-based diary

*CFQ-R* Cystic Fibrosis Questionnaire-revised, *CPET* cardiopulmonary exercise test, *FEV*_*1*_ forced expiratory volume in 1 s, *FVC* forced vital capacity, *RV/TLC* residual volume/total lung capacity, *VO*_*2peak*_ peak oxygen uptake, *Watt*_*max*_ maximal aerobic power

^a^only in patients without cystic fibrosis related diabetes

^b^only in European centers

^c^selected centers only

^d^US centers only

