## Methods

### Study design

This study is an international multi-centre, randomised controlled trial with a parallel group design (Clinical trials.gov Identifier: NCT01744561). The study is conducted across CF centers in eight countries (Austria, Canada, France, Germany, Netherlands, Switzerland, United Kingdom and the United States). Patients are randomly allocated to either a partially supervised PA intervention or control intervention (no PA), see Fig. 1. Due to the nature of the intervention, blinding of participants is not possible. However, blinding of care team members and controls with respect to measurement results are done whenever possible. The study is conducted in full conformance with the principles of the “Declaration of Helsinki” (as amended in Tokyo, Venice and Hong Kong) and with the EC/ICH-Guidelines on Good Clinical Practice. The study is restricted to patients who provided written informed consent.

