### Randomisation

Participants are randomly allocated to the intervention and control group in a one-to-one ratio using block-randomisation (block sizes of 4) and stratified by country and according to whether FEV_1_ is below or ≥70% predicted (moderate/severe lung disease vs. normal/mild lung disease) [12]. A person not involved in the study created a computer-generated randomisation list that was implemented into the database (REDCap, Research Electronic Data Capture) by a person from the Clinical Trials Unit Bern, Switzerland, offering administrative database support. Randomisation is done at each study site within the database (REDCap Software-Version 5.9.2 – © 2014 Vanderbilt University Belgium) allowing complete allocation concealment. The participant’s mean FEV_1_ value in % predicted from both baseline visits (1a and 1b) is entered and a group allocation is returned automatically. We implemented a training database with identical electronic case report forms (eCRF’s) and data collection instruments to allow study site investigators to familiarise themselves with the database before entering real patient data. The database allows entering patient data on-line from different study sites into eCRF’s. As lung function and clinical status are fundamental in this study and may change within short time periods, the intervention starts immediately after randomisation has taken place.

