The secondary efficacy endpoints will be analysed according to the main model described above. This includes the 0 to 6 months and the 0 to 12 months’ time periods for most variables, and the effects of the intervention on the change in FEV_1_ over 12 months, and the change in FEV_1_ between month 6 and month 12. Likewise, the change in glucose levels 1 and 2 h after a standardised glucose load between baseline and 9 months will be compared between groups. The endpoint “time to first exacerbation” will be analysed using a Cox proportional hazard model, while Poisson regression will be used for “number of upper respiratory tract infections”. The frequency of study participants developing diabetes mellitus between baseline assessments and 9-months follow-up will be compared between groups using chi square statistics. For safety endpoints, data will be monitored throughout the study for all patients. Analysis will be performed on total number of events and type of event (fracture, sprain, hypoglycaemia, haemoptysis, pneumothorax, etc.). The change from 6 to 12 months for all secondary outcomes and for the other explorative endpoints will be analysed with the main model described above except for “days on oral / intravenous antibiotics” which will be analysed using Poisson regression.

For the main analysis, the statistician and the PI will have full access to the dataset including the DSMB. Later, for secondary analysis, data will be shared among national coordinators.

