### Limitations

Due to the nature of a partially supervised study, adherence to PA and data entries in the web-based diary cannot be fully controlled. However, objective measures of exercise capacity using CPET and PA (substudy using Actigraph accelerometry) will be used to verify training effects after 6 and 12-months and will provide an indication of whether study participants adhered to their training schedule or not. Blinding of study participants to minimise bias is not possible in PA intervention studies, but outcome assessors are blinded, whenever possible. A selection bias towards a physically active CF population may occur, because patients who are physically active in their daily lives might be more likely to participate in this trial.

Patient recruitment for long-term PA interventions is challenging [5], in particular in rare diseases such as CF. Moreover, there are several recent drug trials on the effects of CF transmembrane conductance regulator corrector and potentiator therapy that might interfere with the ACTIVATE-CF trial. Major efforts have been done with respect to study center recruitment. The study is currently running in > 20 specialised CF centers in eight countries in Europe and Northern America. The first study participant was enrolled in June 2014 and the last study participant is expected to complete the last study visit in June 2018.

This study could make an important contribution to the knowledge on the effects of regular vigorous PA on several important health outcomes in CF. In particular, the use of modern PA monitoring and motivational feedback embedded in the intervention will enhance our understanding on the feasibility and usefulness of these tools with respect to long-term PA adherence.

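### The only listed safety endpoint is filtered by the investigator's judgement of relation to exercise, so by-arm counts can mix attribution with incidence

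*Protocol article*

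**What the plan says.** **Endpoint.** In Study endpoints and measurements, Table 2 has one row under safety: "Adverse events at least possibly related to exercise (e.g., sprains, fractures etc"). Its measurement column reads "Judged by investigator".

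**Collection.** Table 1 (Recruitment and study procedures) schedules adverse events at every visit for all participants, without a relatedness condition.

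**Analysis.** Statistical analysis says of the safety endpoints: "Analysis will be performed on total number of events and type of event". It gives haemoptysis, pneumothorax, hypoglycaemia, sprain and fracture as examples of types.

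**Who knows the arm.** Study design states: "Due to the nature of the intervention, blinding of participants is not possible". For others it says that "blinding of care team members and controls with respect to measurement results are done whenever possible". Limitations adds that "outcome assessors are blinded, whenever possible". Under Randomisation, "Randomisation is done at each study site within the database", and the baseline lung function value "is entered and a group allocation is returned automatically".

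**The concern.** The filter that decides whether an event counts is a causal judgement about exercise, and exercise is the randomised exposure. One arm is asked to add at least 3 hours of vigorous activity per week; the other is asked not to change its activity. Someone who knows this, and who has activity logs for one arm only, has more reason to call an ambiguous event possibly related in that arm. This needs no carelessness, because knowledge of exposure is a normal input to a causality judgement.

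At stake is what the safety result means. A higher count in the intervention arm could reflect more events, more attribution, or both. Conversely, an event caused by the programme but put down to the underlying disease would drop out of the endpoint. The abstract says that a successful programme would be offered more widely, so a safety summary that does not depend on attribution is worth having.

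**Working it through.** No figure in the document depends on this point, so there is nothing to reproduce. The check compares the passages and then works a short illustration.

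**Step 1: does a causality filter define the endpoint?** Yes. Table 2 states it, so this is not a detail left to an unseen analysis plan.

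**Step 2: does the analysis text remove the filter?** Not as written. The sentence on totals and types follows directly from a reference to the safety endpoints and does not say that causality is disregarded. Two readings are possible:
- It counts Table 2 events only, and the filter applies.
- It counts all adverse events, and it then disagrees with Table 2.

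The text needs an edit under either reading.

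**Step 3: is the judgement masked?** No passage says so.
- The Study design statement on care teams concerns measurement results, not allocation, and is conditional.
- The Limitations statement on outcome assessors is also conditional and mentions neither adverse events nor relatedness.
- The site obtains the allocation from the database, and its staff then counsel intervention participants and review their logs.

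**Step 4: where is there room for attribution to differ?** For a sprain during sport or an exercise test, the link to exercise is plain in either arm and there is little room. Haemoptysis and pneumothorax also occur in cystic fibrosis without exercise; Study population excludes patients with a recent major episode as unstable. There the judgement is discretionary.

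**Step 5: how large could the effect be?** Let r be the true event rate in an arm and q the probability that an event is judged at least possibly related. The counted rate is r × q, so

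counted ratio = (r_int / r_con) × (q_int / q_con).

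With equal true rates the first factor is 1. The document gives no values of q; those below are assumptions.

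| q intervention | q control | Counted ratio |
|---|---|---|
| 0.50 | 0.50 | 0.50 / 0.50 = 1.00 |
| 0.60 | 0.45 | 0.60 / 0.45 = 1.33 |
| 0.70 | 0.40 | 0.70 / 0.40 = 1.75 |

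The formula also works in the other direction. If attribution were 0.45 versus 0.60, the factor would be 0.75, and a true ratio of 1.33 would appear as 1.33 × 0.75 = 1.00. These ratios are not turned into a false-positive rate, because the article names no safety test.

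**The case against.** The case on the other side has real substance.

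- **No between-arm safety test is specified.** Statistical analysis names a group comparison for glucose and for new diabetes, but not for adverse events. A reader might infer that a biased formal comparison is planned; the text does not support that. What stands is that any by-arm table of this endpoint carries the attribution.
- **The investigator is not stated to be unblinded.** A reader might take this as fact. It is an inference, though a strong one given who receives the allocation and how conditional the blinding statements are.
- **The criterion is relation to exercise, not to the programme.** Controls may be active, since only more than 4 hours of vigorous activity per week excludes, and they undergo the same exercise tests. The threshold is also inclusive. This narrows the problem for sprains and fractures, less so for haemoptysis and pneumothorax.
- **Other harms escape the filter.** Exacerbations, unplanned hospitalisations and new diabetes are recorded separately. Serious safety issues go to the monitoring board within 72 hours, and the early-termination rule for serious adverse events has no relatedness condition. It would be too strong to say that respiratory or glycaemic harm would go unseen.
- **Counting totals.** A reader might infer that repeat events in one patient dominate, or that unequal follow-up is ignored. The article says neither, and such tabulation detail commonly belongs to the analysis plan.

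**Conclusion.** The point holds in a limited form. As defined in Table 2, the sole safety endpoint depends on an investigator's attribution to the randomised exposure, with no masking of that judgement described, and the analysis text does not say that events are counted whatever their cause. A by-arm display of the endpoint can therefore mix attribution with incidence, chiefly for events with a background rate in cystic fibrosis.

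This rests on one inference, that whoever judges relatedness usually knows the arm. Neither the direction nor the size of any bias can be established from the document; the ratios of 1.33 and 1.75 follow only from assumed attribution probabilities. The primary endpoint is not affected. The change is worth making because it is cheap and removes an avoidable ambiguity.

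**What to change.** 1. In Table 2, define the safety endpoint as all adverse events and all serious adverse events, presented by arm, whatever the attribution.
2. In Statistical analysis, state that totals and types are counted irrespective of causality, using the event types already named there, so that the two sections agree.
3. Keep investigator-judged relation to exercise as a descriptive secondary tabulation.

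The cost is a change of wording; adverse events are already collected at every visit in both arms. The drawback is a noisier comparison, because background disease events enter both counts.

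The change removes attribution only. The scheduled calls are described for the intervention arm alone, so the chance of learning about an event may still differ between arms; that is a separate matter to bear in mind when reading the table.

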#### Pulmonary function

Spirometry and body plethysmography is performed according to ERS and ATS guidelines [14, 15] at all study visits pre-bronchodilation. FEV_1_ and forced vital capacity (FVC) are expressed as %predicted using reference values published by Quanjer et al. [12]. The degree of air trapping (Residual Volume/Total Lung Capacity) is derived from lung volumes.

#### Cardiopulmonary exercise testing (CPET)

A continuous incremental cycle ergometer cardiopulmonary exercise test using the Godfrey protocol [16] is performed in accordance to a statement on exercise testing in CF [17]. Maximal aerobic power (Watt_max_) and VO_2_peak will be expressed in percent of predicted [16, 18].

#### Physical activity

Daily PA is measured using a tri-axial Omron HJ-322 pedometer for 7 days prior to baseline visit 1b and prior to the 6-months and 12-months visits. The 7-day recall questionnaire is used to assess time spent in the PA categories ‘hard’ and ‘very hard’. The questionnaire is a feasible and valid instrument to assess PA in people with CF [19].

#### Health-related quality of life (HRQoL)

HRQoL is assessed using the adolescent/adult version of the Cystic Fibrosis Questionnaire (CFQ-R), a validated CF-specific instrument [20, 21].

#### Psychological health

Psychological health is assessed using the Depression Anxiety Stress Scales (DASS), a 42-item self-report questionnaire that has been validated in clinical and non-clinical samples [22, 23].

#### Glycaemic control

Assessment of glycaemic control and potential diagnosis of cystic fibrosis related diabetes (CFRD) is performed using the oral glucose tolerance test after an 8 h fast according to a published consensus statement [24]. Blood samples are collected in a fasting state, and 1 and 2 h after the glucose challenge.

#### Exacerbations

Time to, number of and time with pulmonary exacerbations with and without hospitalisations, number of pulmonary exacerbations requiring intravenous antibiotic treatment, number of days on intravenous antibiotic therapy for pulmonary exacerbations and time to first intravenous antibiotic treatment for pulmonary exacerbations are assessed. The information is derived from a diary kept by each participant, 3-months retrospective questionnaires completed at each study visit, interviews at each study visit and scheduled telephone contact, and information provided by the participants at participant-initiated contacts. Each episode of pulmonary exacerbation defined as new or changed antibiotic therapy based on modified Fuchs criteria is recorded [25]. In addition, we note the number and times of outpatient visits to a medical doctor, clinic or hospital for CF-related complications with documentation of reasons. This includes the number of unplanned hospitalisations and their respective duration and reasons.

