**Methods/design:**

It is planned that a total of 292 patients with CF 12 years and older with a FEV_1_ ≥ 35% predicted shall be randomised. Following baseline assessments (2 visits) patients are randomised into an intervention and a control group. Thereafter, they will be seen every 3 months for assessments in their centre for one year (4 follow-up visits). Along with individual counselling to increase vigorous PA by at least 3 h per week on each clinic visit, the intervention group documents daily PA and inactivity time and receives a step counter to record their progress within a web-based diary. They also receive monthly phone calls from the study staff during the first 6 months of the study. After 6 months, they continue with the step counter and web-based programme for a further 6 months. The control group receives standard care and keeps their PA level constant during the study period. Thereafter, they receive the intervention as well.

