Participants receive further motivation by being equipped with a three-axial pedometer (Omron HJ-322 U-E). Participants are instructed to wear the pedometer on a daily basis and they are asked to complete a web-based log (http://www.activate-cf.org/) on a daily basis. The user interface of the website is programmed to allow access from classical personal computers, palm tops, tablets and smartphones. Participants are asked to document daily steps from their pedometer and training activities in their web-based logbook, using an individual pseudonym login that is provided by their study centre. In the web-based log book, data on i) vigorous PA’s performed that day (type of PA, duration), ii) total daily step count and exercise step count (steps with estimated energy expenditure of at least 3 metabolic exchange units-METS), and iii) time in sedentary activities (i.e. watching TV, playing video games without activity components, computer time, driving, taking a nap/sleeping) are entered.

The central monitoring unit in Wuerzburg, Germany is responsible for monitoring data entries on the web-based log. The participant’s CF centre will be notified if there have been no completed entries into the system for the previous 3 days or longer. The participants receive a “reminder” message on his or her mobile phone or via email if no entries have been made for three consecutive days. If there are no entries for a whole week, participants are contacted by phone from their centre’s designated activity contact person (i.e., physiotherapist, exercise specialist).

Participants complete a PA questionnaire at all clinic visits. The web-based training logs are checked at the clinic visits and discussed with the participant by the physiotherapists/exercise specialist. The physiotherapist/exercise specialist utilises this information, along with the web-based logs and the interview to provide exercise counselling at every visit to the centre. If necessary, a new activity plan will be created.

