There are scheduled phone contacts after 1, 2, 4 and 5 months by the physiotherapist/exercise specialist into the training to discuss progress and to re-counsel the participants PA plan. During the monthly scheduled telephone contacts, the participant is asked about his or her weekly exercise activities and the written activity agreement is reviewed. Likewise, the web-based activity log is discussed with the participant. If one or more goals of the plan have not been met or problems have been encountered or new activity ideas come up, the plan is modified. The structured interview forms available for the initial counselling are used to assist as needed. In case of admission to the hospital, physical exercise is included in the in-patient treatment (the treating physician needs to decide what is possible).

After the six-month assessment, participants of the intervention group will keep their pedometers and still have access to the web-system to report and view their PA data. Centre staff meets with participants as part of routine care and as deemed necessary by the treating physician. Staff members do not receive the data collected, unless clinically relevant, such as a change in glycaemic control, and advise the patient based on the information that they gather from the patient.

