#### Upper respiratory tract infection (URTI)

As exacerbations, URTIs are identified from participants’ diary, from 3-months retrospective questionnaires completed at all clinic visits, from interviews at study visits and from telephone contacts. URTI are defined as at least 3 consecutive days of runny nose and sore throat.

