#### Courses of unscheduled antibiotics

Antibiotic use is documented at all clinic and study visits as well as in participants’ diaries and antibiotics courses (intravenous, oral or inhaled) are counted. In case of exacerbation, planned study visits are postponed until 14 days after oral or intravenous antibiotic treatment of exacerbation has been stopped.

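### Exacerbations, respiratory infections and antibiotic days are taken partly from telephone contacts, but scheduled calls are described for the intervention arm only; the passages need reconciling and between-arm counts should rest on shared sources

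*Protocol article*

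**What the plan says.** **Telephone contact as a data source.** The Exacerbations section draws on the participant diary, the 3-month retrospective questionnaire, "interviews at each study visit and scheduled telephone contact", and contacts that the participant initiates. The URTI section identifies infections from the diary, the questionnaire, and "from interviews at study visits and from telephone contacts". Table 2 gives the measurement for both URTI number and antibiotic days as "3-months retrospective questionnaire, Interviews, Diary and telephone calls".

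The sources do not fully agree with each other. The section on courses of unscheduled antibiotics does not mention the telephone: "Antibiotic use is documented at all clinic and study visits as well as in participants" (the sentence goes on to diaries). Table 2 likewise gives questionnaire and physician assessment for time to first exacerbation, without calls, although the Exacerbations section lists them.

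**Who is called.** Under Intervention arm: "There are scheduled phone contacts after 1, 2, 4 and 5 months by the physiotherapist/exercise specialist". The abstract says of the same group: "They also receive monthly phone calls from the study staff during the first 6 months of the study". That arm is also telephoned when the web log lapses: "If there are no entries for a whole week, participants are contacted by phone". For controls the abstract says "The control group receives standard care and keeps their PA level constant during the study period", and the Control arm section describes no calls.

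**The ambiguous place.** In Table 1, footnote c (each visit and scheduled telephone contacts) is attached to the exercise motivation interview, which is for the intervention group only. It is also attached to the interview in a row above that heading, which covers all participants.

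**The concern.** A between-arm comparison of event counts assumes that an event has the same chance of being recorded in either arm. Here one of the named sources is, as far as the article shows, a feature of the intervention. An event that the diary, the 3-month questionnaire and the visit interview all miss can still be counted if it comes up in a call, and only the intervention arm is described as having such calls. Participants are not blinded, so blinding does not offset this.

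The Statistical analysis section plans a Cox model for time to first exacerbation (secondary) and Poisson regression for URTI number and antibiotic days (both explorative). Neither model, as described, separates a higher event rate from better detection. The excess would fall on the intervention arm, so a real reduction could be hidden or a harm suggested where none exists.

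**Working it through.** **1. Contacts, counted from the article.** Visits are at months 3, 6, 9 and 12 in both arms; described calls are at months 1, 2, 4 and 5 in the intervention arm.

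| Period | Intervention | Control |
|---|---|---|
| Months 0-6 | 2 visits + 4 calls = 6 | 2 visits = 2 |
| Months 6-12 | 2 visits = 2 | 2 visits = 2 |
| Months 0-12 | 8 | 4 |

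Lapse-triggered calls are left out because they are not scheduled. The Exacerbations section counts only scheduled contact; the looser URTI wording might take them in.

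**2. Exposure by endpoint.**
- *URTI number (explorative):* self-reported, defined by at least 3 consecutive days of symptoms, with telephone named in both the text and Table 2. Most exposed.
- *Antibiotic days (explorative):* telephone named in Table 2 only.
- *Time to first exacerbation (secondary):* telephone named in the text only. The definition requires new or changed antibiotic therapy, which is harder to overlook than a cold. Less exposed.
- *Adverse events:* no passage names calls as a source. Table 1 records them at visits, and Table 2 leaves the judgement to the investigator.
- *FEV1 (primary):* spirometry at visits. Not measured through calls.

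**3. Illustration of size, for URTI number only.** The article gives no event rate or capture figure for these endpoints, so there is no stated figure to reproduce.

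Inputs from the Sample size calculation section: 292 randomised 1:1 with 20% dropout, so 292 × 0.8 / 2 = 116.8, about 117 per arm. Assumed: r = 1 or 2 recorded control URTIs per patient-year; extra capture x = 10%, 20% or 30% in the intervention arm during months 0-6 and none after; no true effect; Poisson counts without overdispersion; two-sided 5% test.

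Over 6 months, expected counts are C = 117 × r × 0.5 (control) and I = C × (1 + x). Over 12 months, C = 117 × r and I = 117 × r × 0.5 × (2 + x). Then SE = √(1/C + 1/I), d = ln(I/C)/SE, and the probability of significance against the intervention is 1 − Φ(1.96 − d). With no bias this is 2.5%.

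Worked case (6 months, r = 2, x = 30%): C = 117, I = 152.1, ln(1.3) = 0.262, SE = 0.123, d = 2.13, probability 1 − Φ(−0.17) = 57%.

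| Window | r | x = 10% | x = 20% | x = 30% |
|---|---|---|---|---|
| 6 months (rate ratio 1.10 / 1.20 / 1.30) | 1 | 8% | 18% | 33% |
| | 2 | 11% | 31% | 57% |
| 12 months (rate ratio 1.05 / 1.10 / 1.15) | 1 | 6% | 11% | 20% |
| | 2 | 8% | 18% | 35% |

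The article fixes no window for the URTI count, so both are shown.

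**The case against.** The strongest reply is footnote c of Table 1. It ties scheduled telephone contacts to an interview row covering all participants, and the Exacerbations section does not limit its telephone interviews to one arm. A journal article condenses a longer protocol, which may schedule the same calls for controls. This stands as a reason not to state flatly that controls are never called. It does not settle the matter: every call that the article actually describes is in the intervention arm.

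Second, controls do not depend on memory alone. Both arms have the diary, the 3-month questionnaire, interviews at each visit and participant-initiated contacts. A call adds an event only if all of these missed it. This stands, and it limits the size by an unknown amount.

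Third, a reader might infer that calls bring exacerbation dates forward, or that adverse events are biased too. The article does not support either. Nothing says that onset is the date of report, so an earlier report of the same course need not move its date. No passage makes calls an adverse-event source.

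Fourth, the capture percentages and URTI rates are assumed, and the larger range uses the 6-month window, where the effect is strongest. This is correct, and nothing has been computed for exacerbations.

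**Conclusion.** The point holds as a contradiction to be reconciled and, if controls are not called, as unequal opportunity for detection: 6 against 2 scheduled contacts in months 0-6, and 8 against 4 over the year. The direction is against the intervention. URTI counts are most exposed, antibiotic days on the strength of Table 2 alone, and time to first exacerbation less so. Adverse events and the primary FEV1 endpoint are not shown to be affected.

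The size is unknown. The ranges of about 8-57% over 6 months and 6-35% over 12 months for false significance against the intervention rest on the assumed extra capture and URTI rates, on 117 analysed per arm and on Poisson variation. They apply to an explorative endpoint only. It would be too strong to conclude that event detection certainly differs by arm or that all event and safety results are distorted.

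**What to change.** 1. State whether controls receive scheduled calls and, if so, when. Bring the Intervention arm and Control arm sections, footnote c of Table 1 and the endpoint sections into line. Reconcile Table 2 with the text on telephone as a source for antibiotic use and for exacerbations.
2. Unless both arms have the same calls, count events for the between-arm comparisons of these endpoints only from sources common to both arms: diary, 3-month questionnaire, visit interviews and participant-initiated contacts.
3. Report an all-sources analysis, including events known only from calls, as a sensitivity analysis. Keep those events for safety monitoring.

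The cost is a flag for the source of each event, which may be hard to reconstruct for participants already followed, since recruitment began in 2014. A few real events drop out of the main counts. The remedy is also incomplete: a call may prompt a participant to make a diary entry, and that effect remains. No visit is added and the primary analysis is unchanged.
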